## Abstract

**Background:**

Although half of all patients with heart failure (HF) have a normal or near-normal ejection fraction and their prognosis differs little from that of patients with a reduced ejection fraction, the pathophysiology of HF with preserved ejection fraction (HF-PEF) is still poorly understood, and its management poorly supported by clinical trials. Sodium and fluid restriction is the most common self-care measure prescribed to HF patients for management of congestive episodes. However, its role in the treatment of HF-PEF remains unclear. This trial seeks to compare the effects of a sodium- and fluid-restricted diet versus an unrestricted diet on weight loss, neurohormonal activation, and clinical stability in patients admitted for decompensated HF-PEF.

**Methods/Design:**

This is a randomized, parallel trial with blinded outcome assessment. The sample will include adult patients (aged ≥18 years) with a diagnosis of HF-PEF admitted for HF decompensation. The patients will be randomized to receive a diet with sodium and fluid intake restricted to 0.8 g/day and 800 mL/day respectively (intervention group) or an unrestricted diet, with 4 g/day sodium and unlimited fluid intake (control group), and followed for 7 days or until hospital discharge. The primary outcome shall consist of weight loss at 7 days or discharge. The secondary outcome includes assessment of clinical stability, neurohormonal activation, daily perception of thirst and readmission rate at 30 days.

**Discussion:**

Assessment of the effects of sodium and fluid restriction on neurohormonal activation and clinical course of HF-PEF can promote a deeper understanding of the pathophysiology and progression of this complex syndrome.

**Trial registration number:**

ClinicalTrials.gov identifier: NCT01896908 (date of registration: 8 August 2013).

## Background

Heart failure (HF) with preserved ejection fraction (HF-PEF), historically known as diastolic HF, is the clinical syndrome characterized by HF with normal or near-normal systolic function [1]. More recent epidemiological studies and registries have suggested that HF with reduced ejection fraction and HF-PEF are equally prevalent, with the latter accounting for 40 to 71% (mean approximately 50%) of cases [2, 3].

The etiology and epidemiology of HF-PEF appear to be distinct from those of HF with reduced ejection fraction. Women and older adults with comorbidities such as hypertension, diabetes, obesity, and coronary artery disease are more commonly affected [4–8].

Despite the importance of HF-PEF, the pathophysiology and treatment of this phenotype of HF are still poorly understood. Thus far, the major clinical trials (I-Preserve, PEP-CHF, CHARM-Preserved, DIG-CHF and TOPCAT trial) [9–13] have failed to demonstrate the efficacy of any specific treatment on mortality in these patients.

Currently, the mainstay of HF-PEF treatment is symptomatic care and management of comorbidities that predispose patients to this condition, including hypertension, diabetes, ischemia, and arrhythmias [14, 15], and include guidance on lifestyle modifications, such as restricted sodium and fluid intake [14, 15]. Sodium restriction is the self-care measure most commonly prescribed to patients with HF, as it appears to be effective in reducing congestion. However, the evidence base for this recommendation is scarce, and the few studies that have been conducted have yielded inconsistent findings [16–25]. Research has focused on the physiological effects of intake of different amounts of sodium, and few have assessed morbidity and mortality outcomes [17–25]. Except for an observational study by Lennie and colleagues [24] that compared number of hospital admissions and emergency department visits between patients with a sodium intake of >3 g/day versus <3 g/day, no studies have evaluated the effects of sodium restriction in patients with HF-PEF; therefore, its role in these patients remains unknown. Recently, however, Hummel and colleagues [26], investigating the effects of the sodium restricted DASH diet, showed an increased urinary aldosterone excretion during low-sodium diet in patients with HF-PEF.

In an attempt to bridge the knowledge gap in patients with decompensated HF-PEF, this trial seeks to compare the effect of a sodium- and fluid-restricted diet versus an unrestricted diet on weight loss, neurohormonal activation, and clinical stability at 7 days or at hospital discharge in patients admitted for decompensation of HF-PEF.

## Methods/Design

### Study design and centers

This is a randomized, parallel trial with blinded outcome assessment. The study population will comprise patients with a diagnosis of HF-PEF who have presented to hospital with HF decompensation. The study will be carried out at Hospital de Clínicas de Porto Alegre (HCPA), Brazil, and take place at the Emergency Department or other inpatient units.

### Inclusion and exclusion criteria

The sample will include adult patients with a diagnosis of HF (and left ventricular ejection fraction >50%) within 36 hours of hospital admission for decompensation of HF – defined as clinical signs of congestion, history of dyspnea and orthopnea in the week before hospitalization, and B-type natriuretic peptide (BNP) levels >100 pg/mL – who agree to take part in the study and provide written informed consent. Patients with an estimated glomerular filtration rate (Modification of Diet in Renal Disease formula) ≤30 mL/minute, those with cardiogenic shock, HF due to valvular disease and those whose survival is jeopardized by another ongoing condition and/or by difficulty adhering to treatment (for example, due to dementia or cognitive deficits) will be excluded.

### Ethical considerations

All procedures were conducted in accordance with the ethical standards for human subject research set forth in the Declaration of Helsinki. Written informed consent shall be obtained from all patients included in the trial. The project was approved by the Research Ethics Committee of Hospital de Clínicas de Porto Alegre (registration number 12–0437) and is registered in the ClinicalTrials.gov database under identification number NCT01896908.

### Sample size

Sample size calculations were carried out in WINPEPI 11.20 (Brixton Health, Israel). We used the weight loss values reported in the studies of Aliti and colleagues [25] and Cardoso and colleagues [27], which assessed weight loss in patients with HF and systolic dysfunction admitted for HF decompensation and congestion. For a significance level of α = 0.05 and a statistical power of 80%, with a standard deviation of 3 kg and a between-group difference in weight corresponding to a weight loss of 2 kg in 7 days, the minimum sample size will be 74 patients (37 randomized to each group).

### Interventions

The control group (CG) will receive the standard hospital diet, which provides approximately 4 g sodium (10 g salt)/day and unlimited fluid intake. The intervention group (IG) will receive an otherwise identical diet restricted to 0.8 g sodium (2 g salt)/day and 800 mL fluids/day until the 7th day of admission or hospital discharge, whichever comes first.

### Study protocol

Patients who meet the inclusion criteria and are eligible will be invited to take part in this trial during their hospitalization. Data will be collected on sociodemographic parameters, clinical variables, results of laboratory tests performed as part of routine patient care (creatinine, urea, potassium, sodium, complete blood count, and BNP on admission), current medications, body weight, and clinical congestion score, and blood will be collected for assessment of neurohormonal activation. Patients will then be randomized to IG or CG.

Once allocation has been completed, the on-call dietitian will be notified so as to change the participants’ meal plan as appropriate. The same dietary prescription will be used for participants in both the IG and CG: *DIET AS PER RESEARCH PROTOCOL. PATIENT WILL RECEIVE DIET UNTIL __/__ OR DISCHARGE. PLEASE DO NOT ALTER DIET.* This practice will be implemented in agreement with the medical staff and with the hospital Department of Nutrition and Dietetics.

A daily check of medical records will be performed to identify modification of any drug prescription. The search for hypotensive episodes will be performed by checking blood pressure every 6 hours and by questioning patients about symptoms of hypotension (dizziness, fainting or lightheadedness) on a daily basis.

Outcomes assessment 30 days after discharge will be carried out at the study facility by means of a face-to-face encounter between the investigators and each participant, at which time a clinical assessment will be performed and blood will be collected for analysis of neurohormonal activation (Figure 1).

**Figure 1 Fig1:**
[figure not shown]
**CONSORT flowchart of the study.** BNP, B-type natriuretic peptide; R, randomization; std., standard.

### Randomization

The randomization will be performed through a simple sequential randomization plan generated online, using the http://www.randomization.com website.

### Blinding

During hospitalization, the medical staff involved in patient care will be blind to group allocation. All clinical assessments during hospitalization and at 30-day follow-up will be conducted by a nurse also blinded to group allocation.

### Variables in the study

#### Clinical variables

##### Clinical congestion score

The clinical congestion score is an instrument composed of seven questions designed to assess signs and symptoms of congestion, including presence of pulmonary crackles, third heart sound, jugular venous distension, peripheral edema, hepatojugular reflux, orthopnea, paroxysmal nocturnal dyspnea, and New York Heart Association functional class. This score ranges from 1 to 22 points, with higher scores being directly indicative of worse congestion [28].

##### Blood pressure and heart rate

Blood pressure and heart rate will be measured by the trial investigators shortly after randomization.

##### Estimation of glomerular filtration rate

The Modification of Diet in Renal Disease formula will be used for estimation of the glomerular filtration rate [29].

##### Left ventricular ejection fraction

The left ventricular ejection fraction will be assessed by means of echocardiography, using the Teichholz method or, if available, the Simpson method.

##### Body weight

Weight will be measured with participants barefoot, wearing minimal clothing, and standing on the center of a digital platform scale, and recorded in a spreadsheet.

##### Medical history

Data on the etiology of HF, history of present illness, past medical history, comorbidities, and current medications will be collected from patient records and checked during the patient interview.

### Demographic variables

A structured questionnaire will be administered to all participants for collection of demographic parameters (age, sex, ethnicity), socioeconomic, and educational data.

### Laboratory variables

Blood samples will be collected by a trained professional at the time of study enrollment, at hospital discharge, and 30 days after discharge. Samples will be centrifuged at 4°C, 3,670 rpm, for 10 minutes and stored in Eppendorf tubes at -80°C for later analysis of neurohormonal activation (renin and aldosterone).

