### Primary outcome

The primary outcome measure shall consist of weight loss at 7 days or discharge.

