### Secondary outcomes

The secondary outcome measures shall consist of:Clinical stability, defined as improvement in symptoms with no evidence of congestion (assessed by congestion score); weight stable for 2 days, with no loss or gain greater than 1 kg (daily weight check); no intravenous HF drugs for 48 hours (daily medication record: diuretics, vasodilators); no increase in diuretics dose for 48 hours (daily medication record).Neurohormonal activation: assessment of neurohormonal activation shall include measurement of serum renin, aldosterone, and BNP levels on admission, at discharge, and at 30 days.Daily perception of thirst: a visual scale (with values ranging from 0 to 10) will be used daily to verify the degree of thirst.Hospital readmission rate for all-causes. Patients shall be followed for 30 days after discharge.

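### The in-hospital renin, aldosterone and BNP sample is timed to discharge, but the assigned diet and the stated objective end at day 7 or discharge, so patients who stay longer have no end-of-diet sample

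*Protocol article*

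**What the plan says.** Four places in the protocol article bear on the timing.

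- **Interventions:** the restricted diet is given "until the 7th day of admission or hospital discharge, whichever comes first". The diet order shown under Study protocol, used for both groups, likewise carries an end date.
- **Background, closing paragraph (objective):** the trial compares the two diets on "weight loss, neurohormonal activation, and clinical stability at 7 days or at hospital discharge".
- **Laboratory variables:** "Blood samples will be collected by a trained professional at the time of study enrollment, at hospital discharge, and 30 days after discharge". The stored samples are for renin and aldosterone.
- **Secondary outcomes:** neurohormonal activation includes "measurement of serum renin, aldosterone, and BNP levels on admission, at discharge, and at 30 days".

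For comparison, the Primary outcome section uses the same window as the diet: "The primary outcome measure shall consist of weight loss at 7 days or discharge".

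**The concern.** The diet and the objective share one end point: day 7 or discharge. The two sections that fix the blood sampling use another: discharge alone. The two end points coincide for patients discharged by day 7 and separate for everyone else. The rule that the diet stops at the earlier of the two dates shows that stays beyond day 7 are foreseen.

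For those patients the only in-hospital follow-up sample falls after the assigned diet has ended, and the article does not say what they eat from then on. The discharge comparison therefore mixes values taken on the diet with values taken off it. If the effect on renin and aldosterone fades once the diet stops, the contrast shrinks, and a null result could mean either no effect or late sampling.

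Analysis cannot cleanly repair this. Whether a sample is off diet depends on length of stay, which arises after randomization and which the diet might itself influence, so dropping the late samples would not leave a clean randomized comparison. The 30-day sample is off diet by design and cannot stand in for the missing one.

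**Working it through.** **1. Sampling against diet**

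| Patient | Assigned diet ends | In-hospital follow-up sample | Sample at end of diet? |
|---|---|---|---|
| Discharged on or before day 7 | Discharge | Discharge | Yes |
| Discharged after day 7 | Day 7 | Discharge | No |

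The mismatch is confined to the second row.

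**2. The plan's own figure**

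Inputs from the Sample size section: difference 2 kg, SD 3 kg, α = 0.05 (taken as two-sided; the section does not say), power 80%.

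- Normal approximation: n per group = 2 × (1.96 + 0.84)² × 3² / 2² = 2 × 7.84 × 2.25 = 35.3, rounded up to 36, or 72 in total.
- With the t distribution: 36.3, rounded up to 37, or 74 in total.

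The stated 74 is reproduced. It concerns weight loss only, and the present point does not touch it. The article states no power, effect or SD for renin, aldosterone or BNP.

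**3. Dilution of the contrast**

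Let p be the share of patients in hospital beyond day 7, and r the fraction of the on-diet effect still present at their discharge sample. Assume the same p and the same on-diet effect across groups and lengths of stay, and an unchanged SD. Then

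expected contrast at discharge = on-diet contrast × m, with m = (1 − p) + p·r = 1 − p(1 − r).

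**4. Illustration on the power scale**

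Take a hypothetical comparison of means with 80% power at two-sided 0.05. Its noncentrality is 1.96 + 0.84 = 2.80, and the diluted power is about Φ(2.80 × m − 1.96). The values of p and r are assumed.

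| p | r | m | 2.80 × m | Power |
|---|---|---|---|---|
| 10% | 0.5 | 0.95 | 2.66 | Φ(0.70) = 76% |
| 10% | 0 | 0.90 | 2.52 | Φ(0.56) = 71% |
| 30% | 0.5 | 0.85 | 2.38 | Φ(0.42) = 66% |
| 50% | 0.5 | 0.75 | 2.10 | Φ(0.14) = 56% |
| 30% | 0 | 0.70 | 1.96 | Φ(0.00) = 50% |
| 50% | 0 | 0.50 | 1.40 | Φ(−0.56) = 29% |

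**5. Cross-check**

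With 37 per group and a standardized effect borrowed from the weight calculation (2/3), the normal-approximation power is 82% undiluted. With r = 0 it is 73%, 52% and 30% at p = 10%, 30% and 50%. With r = 0.5 it is 78%, 68% and 58%. The pattern is the same.

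**The case against.** **Discharge may be shorthand.** The Abstract says patients are followed for 7 days or until discharge, and in a condensed article the sampling sections may use the word loosely for the end of that window. Figure 1 is cited directly after the description of blood collection, and its legend lists BNP, but the figure is not available, so a day-7 draw cannot be excluded. This limits what can be said about practice. It does not remove the mismatch: two sections independently omit day 7, and a day-7 draw in the figure would itself contradict them.

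**The size is unknown.** This stands in full. Length of stay, neurohormonal effect, SD, rate of fading and diet after day 7 are all absent from the article. A reader might infer that the contrast is certainly biased toward zero, that power really drops to 50% or 29%, or that the loss is worse in sicker patients. The documents support none of these. Dilution is conditional on the effect fading, the two low power figures assume that it vanishes completely, and the 80% starting point belongs to the weight calculation. That longer-stay patients are sicker is plausible, but the article does not say so.

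**The outcome is secondary.** This also stands. Neurohormonal activation is one of four secondary outcomes, although it is named in the objective. The weight outcome, the sample size and the randomized comparison are untouched.

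**Moving the draw has a cost.** Also true: the discharge value, which Secondary outcomes names as a time point, would be lost for long-stay patients unless it is kept as well.

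**Conclusion.** The concern holds for patients who stay beyond day 7. As written, the sampling schedule in Laboratory variables and Secondary outcomes matches neither the diet period in Interventions nor the objective in the Background, and these patients have no sample at the end of the assigned diet.

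If the effect fades off diet, the in-hospital contrast in renin, aldosterone and BNP is multiplied by 1 − p(1 − r). Over the assumed range above, the consequence runs from slight to serious, and the documents do not allow it to be narrowed. The power figures are a scale for judging this, not a property of the trial. It would go too far to say that the trial has no on-diet neurohormone data, since patients discharged by day 7 are sampled on diet.

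Severity: should fix, secondary outcome only.

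**What to change.** Reconcile Laboratory variables and Secondary outcomes with the objective and with Interventions. Time the second blood draw to the end of the assigned diet (day 7 or discharge, whichever is earlier), use that sample for the in-hospital neurohormonal comparison, and keep the 30-day draw. This changes only when blood is taken; the diet itself is not altered.

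**Cost:** a short amendment with the same number of draws. Patients staying beyond day 7 lose the discharge-day value unless it is also kept, which would mean one extra draw for them.

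**Patients already studied:** Trial status reports 13 completed. Against the minimum of 74, that leaves 74 − 13 = 61 planned patients not yet completed. Among the completed patients, flag any sample drawn after the diet ended, and state in the report that the earliest patients may have a different sampling time.

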#### General blood work

General blood work will comprise of complete blood count, urea (ultraviolet kinetic assay), serum creatinine (Jaffé method), plasma sodium and potassium (ion selective electrode).

#### B-type (brain) natriuretic peptide

Immunofluorescence methods will be used for quantitation of BNP in plasma.

#### Renin

A radioimmunoassay for measurement of angiotensin I generated by the action of renin on its substrate, angiotensinogen, will be used for quantitation of plasma renin activity.

#### Aldosterone

A solid phase radioimmunoassay based on aldosterone-specific antibodies will be used for quantitation of serum aldosterone levels.

### Primary outcome

The primary outcome measure shall consist of weight loss at 7 days or discharge.

### Secondary outcomes

The secondary outcome measures shall consist of:Clinical stability, defined as improvement in symptoms with no evidence of congestion (assessed by congestion score); weight stable for 2 days, with no loss or gain greater than 1 kg (daily weight check); no intravenous HF drugs for 48 hours (daily medication record: diuretics, vasodilators); no increase in diuretics dose for 48 hours (daily medication record).Neurohormonal activation: assessment of neurohormonal activation shall include measurement of serum renin, aldosterone, and BNP levels on admission, at discharge, and at 30 days.Daily perception of thirst: a visual scale (with values ranging from 0 to 10) will be used daily to verify the degree of thirst.Hospital readmission rate for all-causes. Patients shall be followed for 30 days after discharge.

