### Statistical analyses

Continuous variables following a normal distribution will be expressed as mean ± standard deviation; asymmetrically distributed continuous variables will be expressed as median and interquartile range; and categorical variables will be expressed as absolute and relative frequencies. For between-group comparisons, Student’s *t-*test will be used for normally distributed variables, and the Mann–Whitney *U* test for asymmetrically distributed variables. A paired *t*-test will be used for within-group analysis of body weight and congestion score. The chi-square or Fisher’s exact tests will be used to evaluate associations between categorical variables. The generalized estimating equations test with Bonferroni adjustment will be used for comparison between variables during the study period. The significance level will be set at 5%, and all data will be analyzed in SPSS 18.0 (SPSS Inc., Chicago, IL, USA).

For assessment of clinical stability, in accordance with pre-established criteria, two blinded examiners (physician HF specialists not involved in the care of the study participants) will analyze the outcome variables in both groups.

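### The named renin and aldosterone comparisons use neither the admission value nor recorded drug use as covariates; the cost is precision and interpretability, not validity

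*Protocol article*

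**What the plan says.** Under Secondary outcomes, "assessment of neurohormonal activation shall include measurement of serum renin, aldosterone, and BNP levels on admission, at discharge, and at 30 days". Laboratory variables gives matching sampling times: enrollment, hospital discharge and 30 days after discharge.

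Under Study protocol, the data gathered before allocation include "current medications, body weight, and clinical congestion score, and blood will be collected for assessment of neurohormonal activation"; randomization follows. The same section provides for a daily check of the records for prescription changes, and Medical history says that current medications are checked at interview. The eligibility criteria set no condition on background drugs. On allocation, "The randomization will be performed through a simple sequential randomization plan generated online", and no stratification factor is named.

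Statistical analyses names Student's t-test or the Mann-Whitney test for between-group comparisons. It then adds: "The generalized estimating equations test with Bonferroni adjustment will be used for comparison between variables during the study period". No covariate is named for any of these, and the section does not say which test serves the hormones.

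**The concern.** Drugs that act on the renin-angiotensin-aldosterone axis, and beta-blockers, are expected on general pharmacological grounds to move renin activity and aldosterone. The documents do not name these classes or give usage rates, so both their use and their effect are assumptions here. If use is mixed, it adds between-patient variation that has nothing to do with diet. Patients also differ in hormone level for many other reasons, and the admission sample captures much of that.

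The trial holds both pieces of information before randomization, yet the tests it names do not draw on them as covariates. The sample size was set for weight alone, so precision for the hormones is whatever is left over. Two things are at stake. A real diet effect on the hormones may be estimated less precisely than the data allow. And a visible difference in drug use between arms would leave the hormone result open to argument, with any adjustment then chosen after the baseline table has been seen.

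**Working it through.** **The plan's own figure.** Inputs from Sample size: alpha 0.05, power 80%, SD 3 kg, difference 2 kg. A two-sided t-based calculation with effect size 2/3 gives 36.3, so 37 per group and 74 in total, as stated (power 80.8%). The normal approximation gives 36 per group, 72 in total. The figure concerns weight; no power is stated for renin or aldosterone. With 37 per arm and no covariate, the hormone effect detectable with 80% power is 0.66 SD.

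**Chance imbalance.** For drug use p and 37 per arm, the difference in proportions has SD √[2p(1−p)/37], which is 0.114 at p = 0.4. From two Binomial(37, p) counts, the probability of a difference of at least 15 points (6 or more patients) is 0.11, 0.16, 0.19 and 0.20 at p = 0.2, 0.3, 0.4 and 0.5. These values of p are assumed.

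**What each analysis leaves as variance.** Work on the log scale, with variance 1 among patients of the same drug status. Assume one class with p = 0.4 that shifts the hormone by k = 1 SD equally at admission and follow-up, and a within-patient correlation r of 0.5 or 0.7 at fixed drug status. The drug variance is V = p(1−p)k² = 0.4 × 0.6 × 1 = 0.24.

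| Analysis | Formula | r = 0.5 | r = 0.7 |
|---|---|---|---|
| Follow-up value alone | 1+V | 1.240 | 1.240 |
| Follow-up value, drug indicator | 1 | 1.000 | 1.000 |
| Change from admission | 2(1−r) | 1.000 | 0.600 |
| Admission value as covariate | (1+V) − (V+r)²/(1+V) | 0.798 | 0.527 |
| Admission value and drug indicator | 1−r² | 0.750 | 0.510 |

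Ratios of these variances translate into equivalent numbers of patients:

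- Admission covariate against follow-up value alone: 1.240/0.798 = 1.55 and 1.240/0.527 = 2.35.
- Admission covariate against change from admission: 1.000/0.798 = 1.25 and 0.600/0.527 = 1.14.
- Drug indicator added to the admission covariate: 0.798/0.750 = 1.06 and 0.527/0.510 = 1.03, a gain of about 6% and 3%.
- Drug indicator when the admission value is ignored: 1.240/1.000 = 1.24; over p = 0.3 to 0.5 this is 1.21 to 1.25.

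**Sensitivity at r = 0.5.** With k = 0.5, V = 0.06 and the drug term adds 0.764/0.750, about 2%. With k = 1.5, V = 0.54 and it adds 0.838/0.750, about 12%.

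**Cost of extra terms.** Estimating q covariates inflates the variance of the arm contrast by roughly (N−3)/(N−q−3). With N = 74, going from q = 1 (71/70) to q = 4 (71/67) costs 70/67 = 1.045, about 4.5%. One class alone would therefore roughly break even against three terms. If three independent classes each had k = 1 and p = 0.4, then V = 0.72. The drug terms would give 0.855/0.750 = 1.14 at r = 0.5 and 0.548/0.510 = 1.07 at r = 0.7, which exceeds that cost.

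**The case against.** The strongest objection is that this is an omission from a condensed article. Covariates for a secondary biomarker are often left to an analysis plan, and GEE is a regression method that could include them. That lowers the weight of the point but does not remove it. The section names specific tests, two of which take no covariates, so it states a choice that can be improved.

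A second objection is that the design already deals with much of the noise. If the GEE is read as a group-by-time contrast from admission onward, a stable drug effect cancels. This stands, and the change-from-admission row above shows it. It does not help a t-test or Mann-Whitney test of the hormone at a single time point, and on the assumptions used a covariate for the admission value still does better than a change contrast.

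Third, pre-randomization drug indicators may describe exposure poorly by discharge or day 30, since prescriptions can change during an acute admission. That also stands and is one more reason to expect a modest benefit from the drug terms.

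A reader might go further and infer that drug imbalance biases the diet comparison or raises its false-positive rate. It does not. Under randomization the imbalance is chance variation already covered by the 5% error rate, so the 19% probability of a 15-point imbalance is not an excess error risk. Nor do the documents support the view that medication is disregarded: it is recorded at baseline and changes are checked daily. The gap lies in its use in the analysis.

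**Conclusion.** The point holds as a minor improvement to a secondary analysis. The named comparisons of renin and aldosterone are valid but do not draw on the admission value or recorded drug use as covariates. They give up precision and are harder to interpret if a drug imbalance is visible.

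Under assumed values (40% use, a shift of 1 residual SD, within-patient correlation 0.5 to 0.7), the admission value supplies most of the gain over a single-time-point test. One drug class adds about 3-6% beyond it, before the cost of the extra terms. It would be tempting to credit drug adjustment with the equivalent of 21-25% more patients, but that holds only if the admission value is ignored. None of the assumed inputs is in the documents, so the ordering of the gains is more dependable than their size. The primary outcome and the total of 74 are untouched.

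**What to change.** State in Statistical analyses that the main hormone comparison is a model of log renin activity and log aldosterone at discharge and at 30 days, by arm, with the log admission value of the same hormone as covariate. This uses data already collected and costs one degree of freedom.

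Add indicators for pre-randomization use of (a) ACE inhibitor or ARB, (b) mineralocorticoid antagonist and (c) beta-blocker. This costs three further degrees of freedom. The reason to fix them in advance is as much to settle the adjustment before the baseline table is seen as to gain precision.

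Tabulate by arm any start, stop or dose change in these classes after randomization. The daily prescription check supplies this for the hospital stay. Do not adjust for these changes in the main comparison, because the diet could influence them.

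The change is a few sentences, with no new data and no change to sample size. Trial status reports 13 patients completed and recruitment continuing, so it can still be specified before the comparative analysis.
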